#### Study visits and clinical monitoring

Following enrollment, participants attend study visits every 4 weeks through week 24, compensated $50 per visit. Each visit includes a symptom-driven physical examination, vital signs monitoring, and adverse event assessment. Laboratory monitoring includes complete blood count and comprehensive metabolic panel at weeks 12 and 24.

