#### Secondary outcomes: effectiveness and safety outcomes

The secondary outcome of effectiveness is incident opioid overdose, defined as participant-reported overdose responding to community-administered naloxone, overdose requiring emergency medical services, or fatal overdose. Fatal overdoses will be ascertained through: (1) review of the San Francisco Medical Examiner records, (2) review of emergency medical services records and hospital systems within San Francisco, and (3) participant emergency contacts who will be contacted if participants miss consecutive study visits. Secondary safety outcomes include the proportion of participants experiencing grade 2 or higher adverse events at least possibly related to study medication, including injection site reactions, hepatic abnormalities, and other adverse events. Grade 2 adverse events are defined as moderate events requiring minimal intervention (e.g., nausea), while grades 3–5 represent severe, life-threatening, or fatal events requiring significant intervention (e.g., opioid overdose) [18]. 

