#### Follow-up assessments

Monthly follow-up visits will include clinical assessment, adverse event monitoring, and collection of biomarkers. At weeks 12 and 24, participants will undergo additional laboratory testing including complete blood count and comprehensive metabolic panels. All participants, regardless of study completion or early discontinuation, will be offered assistance to receive provider-prescribed naltrexone at study conclusion which is possible via public insurance in California. A final assessment at week 32 will evaluate incident overdoses and adverse events via telephone interview.

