### Analysis plans

#### Sample size and power

The sample size calculation is based on the primary quantitative outcome of retention (acceptability). With 50 participants per arm, the study has 85% power to detect a 25% difference in retention between groups (α = 0.05). The baseline incidence of unintentional opioid overdose is unknown, precluding formal power calculations for effectiveness outcomes. However, prior research in our population of intereset suggests opioid overdose mortality rates of approximately 5% over 12 months among people living with HIV who use stimulants, suggesting our sample should provide adequate sensitivity to detect preliminary effectiveness signals [19]. Observation of 4.72 incident overdoses in the usual care group (12% over 24 weeks) and 0 overdoses in the intervention group would provide 80% power to reject the null hypothesis of equivalent overdose risk between groups.

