#### Effectiveness analysis (Secondary)

Time-to-event analysis using Kaplan-Meier methods will evaluate cumulative probability of first opioid overdose. Cox proportional hazards models will estimate overdose risk adjusting for key covariates including age, race/ethnicity, housing status, and HIV status. Safety analyses will compare the proportion of adverse events between arms using exact methods for binary outcomes and regression models for continuous safety measures.

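### Safety is compared as crude proportions that ignore observed time, so early loss from the naltrexone arm would understate its 24-week adverse-event risk and leave some participants with no scheduled liver test

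*Protocol article*

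**What the plan says.** The section on secondary outcomes defines the safety outcome as the "proportion of participants experiencing grade 2 or higher adverse events at least possibly related to study medication", and names injection site reactions and hepatic abnormalities among the components. The section Effectiveness analysis (Secondary) gives the method: "Safety analyses will compare the proportion of adverse events between arms using exact methods for binary outcomes". It speaks of a proportion of events where the outcome definition speaks of a proportion of participants; I read it as participants. The same paragraph gives overdose a Kaplan-Meier and Cox analysis.

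On ascertainment, Study visits and clinical monitoring sets visits every 4 weeks to week 24 and says: "Each visit includes a symptom-driven physical examination, vital signs monitoring, and adverse event assessment". For laboratory tests: "Laboratory monitoring includes complete blood count and comprehensive metabolic panel at weeks 12 and 24". A further panel is done at screening. Follow-up assessments adds: "A final assessment at week 32 will evaluate incident overdoses and adverse events via telephone interview".

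On retention, Sample size and power states that with 50 per arm the trial has "85% power to detect a 25% difference in retention between groups". Missing data and sensitivity analyses commits the primary analyses to intention-to-treat and provides for multiple imputation where appropriate, without tying it to safety.

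**The concern.** A crude proportion gives a participant seen once and a participant seen six times the same weight in the denominator. An event after the last attended visit enters the numerator only if another source captures it. If people leave the naltrexone arm early, its recorded proportion therefore falls below the risk over 24 weeks of follow-up. The gap is sharper for hepatic abnormalities: someone who leaves before week 12 has no scheduled post-baseline panel at all.

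This matters because naltrexone is being offered preventively to people who do not use opioids, and the Discussion presents the pilot as groundwork for a definitive trial. An understated harm estimate would be carried forward. An exact test deals with small numbers; it does not correct for unequal observation.

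**Working it through.** **Inputs from the protocol article:** 50 participants per arm; six visits at weeks 4, 8, …, 24; post-baseline panels at weeks 12 and 24; a 25% retention difference, read as percentage points, with 85% power at α = 0.05.

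**Assumptions, since the article gives no figures:** 24-week retention in the naltrexone arm of 65%; dropout uniform over 24 weeks; each person observed to the last attended visit; a true 24-week event risk of 30% with constant hazard; dropout unrelated to events; no recovery by the week-32 call unless stated.

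**1. The plan's own figure.** No base retention is stated, so 85% can be matched only under an assumed one. The two-sided normal-approximation power for two proportions with 50 per arm is 84.9% for 64% v 89%, 86.1% for 65% v 90%, and 74.0% for 50% v 75%. The stated figure is attainable. 65% is used below as the lower retention in a pair close to it.

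**2. Mean observed time at 65% retention.** Those who drop out are last seen at week 0, 4, 8, 12, 16 or 20 with equal probability, a mean of 10 weeks.

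0.65 × 24 + 0.35 × 10 = 15.6 + 3.5 = 19.1 weeks of 24.

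At 90% retention: 0.90 × 24 + 0.10 × 10 = 22.6 weeks.

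**3. Recorded risk.** The risk by visit k is F(k) = 1 − 0.7^(k/6). For k = 0 to 5 this is 0, 0.0577, 0.1121, 0.1633, 0.2116 and 0.2571, with mean 0.1337.

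Recorded proportion = 0.65 × 0.30 + 0.35 × 0.1337 = 0.195 + 0.0468 = 0.242.

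A true 30% appears as about 24%, or 12.1 instead of 15 participants per 50. This is roughly one-fifth low (1 − 0.242/0.30 = 0.19). With a constant dropout rate instead of uniform dropout, the figure is 23.8%.

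**4. Sensitivity at 65% retention and a true risk of 30%.**

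| Change in assumption | Recorded |
|---|---|
| Base case (uniform dropout) | 24.2% |
| All dropouts last seen at week 4 or 8 | 22.5% |
| 60% of events in the first 4 weeks (constant dropout rate) | 26.2% |
| Call recovers half of missed events: 24.2 + 0.5 × 5.8 | 27.1% |
| Call recovers all missed events | 30.0% |

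The week 4 or 8 row is 0.65 × 0.30 + 0.35 × (0.0577 + 0.1121)/2 = 0.225.

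**5. Liver panels at 65% retention.** No scheduled post-baseline panel: 0.35 × 12/24 = 17.5%. Share of the two scheduled panels obtained: (82.5% + 65%)/2 = 73.75%. A telephone call cannot supply these results. At 90% retention the figures are 5% and 92.5%.

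**6. Does observed time repair the estimate?** Per 50 participants in the base case there are 12.1 first events over 209.5 event-free 4-week intervals that were observed. The rate is 12.1/209.5 = 0.0577 per interval, and the Kaplan-Meier risk is 1 − (1 − 0.0577)^6 = 30.0%. The true value is recovered, but only because dropout was assumed unrelated to events.

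**7. The between-arm test.** If both arms had a true 30% risk, with 65% v 90% retention and a constant dropout rate, the crude proportions would be 23.8% v 28.3%. Fisher's test would then reject in 5.3% of trials, against 3.1% with no dropout. This scenario illustrates the mechanism only. It does not describe the stated endpoint, because usual care receives no study medication.

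**The case against.** **Other ascertainment exists.** It would be wrong to infer that events can be seen only at attended visits. The week-32 interview covers adverse events, and consent covers medical record review. This stands for clinical events: recovery of half the missed events would halve the shortfall. It does not stand for liver tests that were never drawn.

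**The 25 points are not a prediction.** A reader might infer that the plan expects a retention gap. It states only the difference it could detect, and gives neither a forecast nor a direction. Retention in treatment and number of visits completed are also listed separately, so stopping injections need not mean missing visits. This stands; the point is conditional on loss of observation.

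**Whichever arm loses more people looks safer.** This symmetrical reading is tempting but poorly supported. The outcome requires possible relatedness to study medication, so the usual-care proportion may be near zero whatever its retention. A near-zero comparator cannot be materially understated, so the claim that better naltrexone retention would overstate its harm largely fails.

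**Untested people counted as normal.** Nothing in the article codes a missing panel as free of hepatic abnormality. The hepatic denominator is not stated and may be settled in an analysis plan that is not shown.

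**Crude incidence is conventional, and censoring has its own assumption.** Kaplan-Meier estimates the risk had everyone stayed under observation, and it is biased if people leave because of harm. Unacceptable toxicity is a listed reason for discontinuation. This stands, and is a reason to report both summaries and to treat such departures explicitly. The generic imputation provision is not a full answer, since it is not tied to safety and an event that was never looked for may not be flagged as missing.

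**Conclusion.** The point holds in a conditional, mainly one-directional form. The stated safety method ignores observed time, while ascertainment depends largely on attendance and, for scheduled liver tests, entirely so. If naltrexone participants leave observation early, naltrexone's 24-week adverse-event risk is understated and the contrast with usual care is biased toward safety. At an assumed 65% retention and 30% true risk, the recorded figure is about 24%. It ranges from about 22% with very early dropout to 26–27% with front-loaded events or half recovery by telephone, and the bias vanishes for clinical events if the call recovers everything. About 17.5% would lack any scheduled post-baseline liver panel under uniform dropout.

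The damage is to the estimate; the effect on false significance is small. Event risk, retention, dropout timing and telephone recovery are all assumptions. The article does not support a stronger reading in which a retention gap is anticipated or the bias applies equally to both arms.

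**What to change.** In Effectiveness analysis (Secondary), keep the exact comparison of crude proportions and add, by arm:

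- Events per observed person-time, or the Kaplan-Meier 24-week risk of a first qualifying grade 2 or higher event, censored at the last adverse-event assessment. Count discontinuations driven by adverse events as events, and state the assumption that other dropout is unrelated to harm.
- Hepatic abnormalities among participants with at least one post-baseline metabolic panel, with the number untested in each arm.
- Events found only at the week-32 call, reported separately.

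This changes analysis wording only, and uses visit and laboratory dates that the scheduled assessments already yield. The costs are slightly wider intervals, a smaller hepatic denominator, and reliance on non-informative censoring for the remaining dropout.

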#### Exposure pattern analysis (Exploratory)

To characterize unintentional opioid exposure, we will implement a multi-level analytical approach comparing self-reported use with biological markers, accounting for their different detection windows. First, we will calculate the prevalence of opioid/fentanyl-positive specimens among participants consistently not reporting intentional opioid use on Timeline Followback (TLFB) interviews.

For urine analyses (with a typical 2–7 day detection window), we will align positive results with the preceding 7-day period in TLFB data to determine potential discordance. This short detection window provides information about recent exposure but may miss intermittent use. We will calculate point prevalence of discordance at each monthly visit, as well as cumulative incidence over the study period. For hair analyses (capturing approximately 30-day exposure history per 1 cm segment) [20], we will implement segmental analysis corresponding to the study’s monthly visit structure. For each monthly segment, we will compare hair results with the corresponding month of TLFB data to identify discordance over longer timeframes. We will calculate both the prevalence of any detectable exposure and quantify concentration levels.

#### Missing data and sensitivity analyses

Primary analyses will use intention-to-treat principles. Multiple imputation will address missing data when appropriate. Sensitivity analyses will include per-protocol analysis and evaluation of different operational definitions of retention and exposure. We will conduct interim analyses for safety monitoring but not for effectiveness unless advised by the appointed Data Safety and Monitoring Board.

## Discussion

The profound loss of life from opioid overdose is particularly concerning when it occurs among individuals who did not intentionally use opioids. Implementing novel overdose prevention strategies for people who use stimulants will be a critical step towards addressing the evolving overdose crisis. We describe an innovative approach that adapts the concept of pre-exposure prophylaxis from HIV prevention to overdose prevention, potentially offering protection against unintentional opioid use. Implementation in a public health research setting will provide foundational data to inform future integration into clinical care, while inclusion of both PWH and those at risk provides an opportunity to reach a population with high rates of stimulant use and demonstrated vulnerability to intentional and unintentional fentanyl use.

The study design offers several methodological strengths. The use of both short-term and long-term biomarkers provides unprecedented insight into patterns of unintentional opioid exposure among people who use stimulants. This comprehensive biological monitoring, combined with detailed qualitative assessment, will help characterize the scope of unintentional use while centering community perspectives on acceptability and implementation. As a pilot trial, this study will provide critical data on baseline overdose incidence in this population to inform power calculations for a future definitive efficacy trial. Additionally, the protocol’s emphasis on harm reduction in both arms ensures that all participants receive overdose prevention services regardless of randomization.

However, several limitations warrant consideration. The single-site design and research setting may limit immediate generalizability, particularly to environments without robust harm reduction infrastructure. Monthly injections could exclude individuals facing significant barriers to regular healthcare engagement, though this mirrors barriers to implementation of other long-acting medications in this population.

This study represents a first step toward expanding the role of medications for primary prevention of opioid overdose. Success of this pilot would demonstrate the acceptability of offering long-acting opioid overdose prevention in settings serving people who use stimulants and provide a scalable model for implementation in similar contexts. Moreover, by targeting a population not eligible for methadone or buprenorphine, this approach could help address a critical gap in current overdose prevention efforts. As the overdose crisis continues to evolve, innovative strategies that account for changing patterns of drug use and market dynamics are increasingly vital.

## Data Availability

No datasets were generated or analysed during the current study.
